We have developed such a protocol, “GAME”, based upon the principles of motor learning and widely accepted EI frameworks including family centred practice [20] and the ecological framework [21]. Data from our recent pilot randomised controlled trial RCT (n = 13) indicates that GAME, a goal-oriented, intensive motor training programme that actively involves parents and includes EE strategies, could be effective in advancing the motor trajectories of infants at high risk of CP [22]. After 12 weeks, GAME intervention infants (n = 6) had an 8.05 point advantage on the Total Motor Quotient of the Peabody Developmental Motor Scales – second edition compared to infants who received standard care therapy (n = 7). Although small, the pilot study confirmed feasibility of recruitment and randomisation procedures, and enabled confirmation of outcome measures and the sample size required for a larger RCT of GAME intervention. This proposed study will address this gap in the literature.

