### Study sample and recruitment

Thirty infants will be recruited from their treating institution, community physician or local therapist. The infants will be recruited in and around Sydney, NSW Australia. Seven NICUs and the Cerebral Palsy Alliance will actively recruiting to this study although infants may be referred from any source. Study sites are listed in the Appendix.

All parents of eligible infants will be informed about the study only after they have had discussions with their medical team regarding the high risk status of their child, or a confirmed diagnosis of CP. Families will be given a site specific information sheet regarding the purpose and design of the study and have opportunity to speak with investigators before consenting to the study. Parents who do not wish to consent to the study will be offered standard community based therapy.

After consent is obtained, prior to randomisation, the investigators will visit the family at home to complete all baseline assessments and collect demographic and perinatal data. MRI and medical data will be obtained from the infant’s medical record.

The Human Research and Ethics Committees of the Sydney Children’s Hospital Network (SCHN), Cerebral Palsy Alliance (CPA) and the University of Notre Dame Australia (UNDA) have approved this study. The experimental design including time points and outcome measures are depicted in the CONSORT [23] flowchart (Figure 1).

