### Sample size

The planned study sample size (n = 30; 15 per group) has been estimated from a power calculation based on our pilot data using motor composite scores of the PDMS-2, with an alpha value of 5% and power of 80%, using a minimal clinically important difference of 10%, accounting for a 20% dropout rate.

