### Outcome measures and procedures

#### Peabody Developmental Motor Scales -Second edition (PDMS-2)

The PDMS-2 [38] is the primary outcome measure in this trial and is a frequently used assessment of motor skills. This test is standardised and normed for children aged from birth to 6 years and has been validated for use as a discriminative measure. Two studies have demonstrated that it is responsive to change in the CP population for both infants [39] and toddlers [40]. It has demonstrated concurrent validity with the GMFM [41] and the Bayley [42]. PDMS-2 assessments will be obtained at baseline, 16 weeks after therapy has commenced and at 12 months and 2 years. Assessments will be blind scored from video.

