### Statistical methods

Analysis will be conducted on an intention-to-treat basis using SPSS and reported according to the CONSORT statement. Descriptive statistics (frequencies, means and 95% CIs) will be used to describe the sample at baseline and data from each outcome measure used will be summarised for both treatment groups. Between-group differences following intervention will be analysed using multiple regression to determine whether group allocation predicts outcome. MRI classification, SES and comorbidities including vision impairment and epilepsy will be considered as covariates in the analysis.

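### The named covariates leave out the pre-randomisation PDMS-2 score, so the 16-week comparison of about 24 infants may give up precision and protection against chance imbalance that would cost almost nothing

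*Protocol article*

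**What the plan says.** The analysis text (protocol article, Statistical methods) is short. Groups are compared after the intervention by multiple regression, to see whether allocation predicts outcome, and "MRI classification, SES and comorbidities including vision impairment and epilepsy will be considered as covariates in the analysis". The word 'including' there expands only the comorbidities. It does not extend the list to motor scores.

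The baseline value of the primary outcome will be available. The PDMS-2 section states that "PDMS-2 assessments will be obtained at baseline, 16 weeks after therapy has commenced and at 12 months and 2 years", and Study sample and recruitment states that after consent and "prior to randomisation, the investigators will visit the family at home to complete all baseline assessments". The Randomization process section confirms that order.

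No change score is mentioned. The randomisation is a plain computer-generated schedule in 30 envelopes, with no stratification by motor level. As far as the text goes, neither the design nor the named covariates account for where an infant starts on the PDMS-2.

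**The concern.** The pre-randomisation value of the primary outcome is usually the first covariate to consider in a small trial. It costs one degree of freedom, needs no new data and corrects for chance differences between arms in starting level. Here it is absent from a list that names other covariates.

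Two things are at stake. If baseline and 16-week PDMS-2 are well correlated, the treatment contrast has a larger standard error than the data require. And if the arms happen to differ in motor level at entry, part of that difference passes into the estimated effect, with nothing in the stated model to remove it.

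**Working it through.** **Inputs from the protocol article.** "The planned study sample size (n = 30; 15 per group) has been estimated from a power calculation based on our pilot data" (Sample size), with 5% alpha, 80% power, a 10% minimal important difference and "accounting for a 20% dropout rate".

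**Assumptions.** The test is two-sided. The correlation r between baseline and 16-week PDMS-2 is not given, so a range is shown. The 0.8 SD effect is illustrative.

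**The plan's own figure.** 30 × (1 − 0.20) = 24 evaluable infants, 12 per arm. The total of 30 cannot be fully reproduced, because no SD is given and the base of the 10% is not stated. With 12 per arm, two-sided 5% and 80% power, it implies a standardised effect of (1.96 + 0.84) × √(2/12) ≈ 1.14 by the normal formula, or 1.20 by the noncentral t.

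**Chance imbalance.** In SD units, the difference in baseline means has standard error √(2/12) = 0.408.
- P(difference exceeds 0.5 SD in either direction) = 2 × [1 − Φ(0.5/0.408)] = 0.22.
- P(difference exceeds 0.25 SD in either direction) = 0.54.
- A 0.5 SD baseline gap shifts the unadjusted contrast by 0.5 × r SD: 0.15 SD at r = 0.3, 0.25 SD at r = 0.5 and 0.35 SD at r = 0.7.

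**Precision.** Adding one baseline covariate multiplies the variance of the contrast by (1 − r²) × [1 + 1/(N − 4)]. With N = 24 this is (1 − r²) × 1.05, and residual degrees of freedom fall from 22 to 21. Power comes from the noncentral t with noncentrality d / √(factor × 2/12).

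| r | Variance factor | SE ratio | Equivalent unadjusted N (24/factor) | Power, d = 0.8 | Power, d = 1.20 |
|---|---|---|---|---|---|
| no adjustment | 1 | 1 | 24 | 47% | 80% |
| 0.3 | 0.91 × 1.05 = 0.956 | 0.98 | 25 | 48% | 82% |
| 0.5 | 0.75 × 1.05 = 0.788 | 0.89 | 30 | 56% | 88% |
| 0.6 | 0.64 × 1.05 = 0.672 | 0.82 | 36 | 63% | 93% |
| 0.7 | 0.51 × 1.05 = 0.536 | 0.73 | 45 | 72% | 97% |

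The standard error breaks even where (1 − r²) × 1.05 = 1, that is r = √(1 − 1/1.05) ≈ 0.22. At r = 0 adjustment costs a little: the SE ratio is 1.02, and power at d = 1.20 is 78%. A simulation of 20,000 trials at each of r = 0, 0.2, 0.3, 0.5 and 0.7 agreed with the d = 1.20 column and with the r = 0 figure.

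**Comparator.** The table compares baseline adjustment with no adjustment. The plan considers other covariates, so the gain over the planned regression is smaller to the extent that MRI class and comorbidities carry the same information. The document gives nothing from which to compute that remainder.

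**The case against.** **The list is not closed.** A reader might infer that the plan rules out baseline adjustment. It does not: the wording is that covariates will be considered, the section is a condensed article's summary, and an unseen analysis plan could add the term. That stands. What remains is that the article names covariates and leaves this one out.

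**The correlation is unknown.** A reader might take baseline PDMS-2 to be almost certainly the strongest predictor. The document does not support that. Infants enter at 3 to 6 months corrected age, and the Background describes a small emergent motor repertoire at this stage and severity that stays largely unknown for much of early childhood. A weak correlation is possible, and at r = 0.3 the gain is only about one percentage point of power. The Background also makes a case for MRI as a predictor of CP, so MRI class is a reasoned choice of covariate.

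**Corrected age and other scales.** A case could be made for a corrected-age term as well. The PDMS-2 is described as normed, so age should add little to a quotient, and a second covariate raises the penalty from 1.05 to 1 + 2/19 = 1.105. A case could also be made for using baseline PDMS-2 in the GMFM-66 and BSID-III analyses. The PDMS-2 section cites concurrent validity with those scales, which does not show that a score in early infancy predicts them at 12 or 24 months. Both objections stand, and neither term is required.

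**Nothing is invalid.** Randomisation keeps the planned comparison unbiased on average. That also stands.

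**Conclusion.** The point holds as an efficiency recommendation. The named covariates omit a pre-randomisation measurement of the primary outcome in a trial expected to analyse about 24 infants, where a baseline gap above 0.5 SD arises in about 22% of randomisations.

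The benefit is substantial if r is 0.5 or more (24 adjusted infants are then worth about 30 or more unadjusted ones), slight at 0.3, and marginally negative below about 0.2. A useful correlation for the same scale 16 weeks apart is plausible but assumed. The figures also assume 12 evaluable infants per arm, a two-sided test and an unadjusted comparator.

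A reader might infer that the primary result would be biased or invalid without this term. The documents do not support that: the loss is in precision and in protection against the imbalance of one particular randomisation.

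**What to change.** Add a sentence to the Statistical methods section that:
- prespecifies the baseline PDMS-2 total motor quotient as a covariate in the primary 16-week regression and in the 12- and 24-month PDMS-2 analyses;
- uses each scale's own baseline where one is collected (COPM, AHEMD-IS, DASS-21);
- keeps the other covariates few and fixed in advance. If the six imaging patterns under Inclusion criteria were entered as categories (5 degrees of freedom), with one each for SES, vision and epilepsy, they would use 5 + 3 = 8 degrees of freedom in about 24 infants.

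Baseline PDMS-2 in the GMFM-66 and BSID-III models can be optional. Corrected age need not be a required term.

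The cost is one sentence and one model degree of freedom, with no new data.

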## Discussion

This paper outlines the design and background for a single blind RCT comparing a novel intervention “GAME” with standard care to improve the motor outcomes of infants at high risk of CP.

## Abbreviations

CP: Cerebral palsy
GMs: General movements
EI: Early intervention
EE: Environmental enrichment
GAME: Goals-Activity-Motor-Enrichment
HP: Home program
PDMS-II: Peabody Developmental Motor Scale -2^nd^ Edition
GMFM: Gross Motor Function Measure
COPM: Canadian Occupational Performance Measure
BSID-III: Bayley Scales of Infant and Toddler Development- 3^rd^ Edition
AHEMD-IS: Affordances in the Home Environment for Motor Development – Infant version
DASS-21: Depression, Anxiety and Stress Scale – 21 version
